## Abstract

**Background:**

There are a high number of adolescents who are at risk of developing an eating disorder. There is, therefore, a strong need to implement prevention programs aimed at reducing the incidence of eating disorders at this critical age. Among other factors, successful prevention programs have been shown to be interactive, carried out by professionals, focused on educational as well as psychosocial elements and have taken risk factors as well as resources into account. The objective of this study protocol is to present the design of a new prevention program for eating disorders in schools.

**Methods/Design:**

The gender-adapted prevention program extends over six school hours. It contains interactive and educational elements about eating disorders and their treatment. Participants pass through different exercises and reflect on the influences of the media, self-esteem, body perception and individual resources. A cluster-randomized controlled trial is chosen to evaluate the program. Based on an estimated effect size of d = 0.3 a total of 1848 participants are enrolled in the study. Eating disorder risk, internalization of Western beauty ideals, body dissatisfaction, self-concept as well as anxiety and symptoms of depression are measured before and immediately after the intervention as well as at a six-month follow-up. In addition, the intervention group evaluates the different components of the program.

**Discussion:**

The study intends to test the practicability and efficacy of an interactive, gender-adapted ED prevention program in schools. Moreover, it will provide valuable information about the occurrence of eating disorder risk factors in school-aged children.

**Trial registration:**

ISRCTN97989348; Registered 19 December 2012.

## Background

The Diagnostic and Statistical Manual of Mental Disorders describes different types of eating disorders (EDs) (DSM-V) [1]: Anorexia nervosa (AN), Bulimia nervosa (BN), Binge Eating Disorder (BED) and Eating Disorders Not Otherwise Specified (EDNOS). What is common to all disorders is a definite disturbance of eating habits or weight control behaviors and patients often transition between fulfilling the criteria for different diagnoses [2]. EDs occur remarkably less frequently than other mental disorders. The 12-month prevalence in the general population of any ED is 0.9% [3]. AN was found to be the most frequent with a 12-month prevalence of 0.7%, followed by a prevalence of 0.2% for BN and 0.1% for BED [3]. Patients suffering from an ED often also suffer from other psychiatric disorders [4] with mood and anxiety disorders being the most common comorbidities [5]. In addition, EDs are often accompanied by severe physical consequences [2]. EDs occur significantly less frequently in males than in females with a proportion of 10% of all cases in AN and BN and 30% in BED [6]. Despite, affected males suffer from similar psychosocial morbidity [7]. As well as the individual burden, the treatment of EDs is also associated with high health care system costs [8].

A multifactorial model of the etiology of EDs is generally accepted in the literature [9] and particular risk factors have been identified. Table 1 provides an overview of well-established risk factors for school-aged children and adolescents (for more detailed information see e.g. [10]).

**Table 1 Tab1:** **Risk factors for Eating Disorders with good empirical support**

Risk factors	Study
**Individual risk factors**	
Female sex	[2,11-13]
Adolescence and childhood	[2,11-13]
Low self-esteem	[11-13]
Perfectionism	[14,15]
Negative emotionality	[11-15]
Body dissatisfaction	[15,16]
**Psychosocial risk factors**	
Internalization of Western beauty ideals	[14,15,17]
Adverse life events (e.g. sexual abuse)	[2,11-13]

Children and adolescents are at particular risk of developing EDs. In AN, for example, there is evidence of two peaks of onset, one before 15–16, the other after 18 years [18]. BN and BED occur later with an average age of onset of approximately 20 years in BN and BED [10]. In addition, the beginning of subclinical levels of eating pathology and disordered eating behavior has been observed in this age range. The German Federal Center for Health Education (BZgA) has reported that more than half of German 13- to 14-year-olds would like to be thinner [19]. Another study with 14- to 18-year-olds showed that 42% of boys and 53% of girls preferred a thin body ideal, 18% of the boys and 19% of the girls were currently trying to lose weight and 17% of the children with a normal weight felt too fat [20]. Moreover, 28.9% of the 11- to 17-year-old girls and 15.2% of the boys showed pathological eating behavior [21]. Such results suggest, therefore, that school age might be an ideal time to implement preventive interventions.

The media might play an important role in the internalization of Western beauty ideals. It is estimated that only one out of every 40.000 women meets the height, weight and body shape criteria of professional models [22], which can lead to body dissatisfaction. This body dissatisfaction is often accompanied by depressive states [23,24] as well as low self-esteem [25] and makes the development of an ED more likely [15].

Schools offer a convenient framework for the implementation of preventive interventions. Children are exposed to social pressure at school which is a significant factor in the development of a negative body image as well as weight concerns in girls and boys alike [26]. Another advantage of schools as the setting for prevention interventions is the possibility to reach a large number of people at the same time. Many previous interventions have only included small samples (for an overview see [27]). Since prevention should benefit individuals as well improve collective health [28], programs should reach as many individuals as possible.

It has been shown that prevention programs developed and conducted in different countries are able to decrease individual ED risk and reduce the occurrence of EDs. In a brief, 8-week, internet-based, cognitive-behavioral intervention in Californian college-age women who were at risk of developing EDs, weight and shape concerns were significantly reduced [29]. Two other intervention programs carried out in the United States for high-school girls with an elevated ED-risk resulted in a significant reduction of bulimic pathology as well as thin-ideal internalization and negative affectivity [30]. On a German national level, Berger, Strauss and colleagues developed and evaluated three different prevention programs in schools. After finishing the programs, the majority of children displayed less alarming eating behavior, greater appreciation of their bodies, increased knowledge about healthy nutrition and EDs as well as raised self-esteem [31-33]. It is important to note, however, that these interventions are time intensive and were evaluated in close cooperation with selected schools.

Taken together there is evidence that ED risk might be positively influenced by preventive interventions. Research has shown that successful ED prevention programs are interactive, selective for risk groups, offered only to females, offered to participants aged over 15 and delivered by professionals [27,34]. However, the young age of onset in AN makes prevention before the age of 15 necessary. In addition, other studies confirmed the “Life-skills” approach [35] which focuses on the improvement of competences in stress- and conflict management as well as strengthening self-esteem and empathy. Preventive interventions need to be able to be integrated in school schedules and address both female and male pupils to reach a broader school population. At the same time, the reduction of risk factors as well as strengthening of existing resources and protective factors should also be included.

### Objectives

The primary aim of this study is to prevent adolescents from developing an ED. To achieve this objective, a gender-adapted prevention program is carried out in schools. The prevention program is interactive and carried out by professionals and based on research regarding the prevention of EDs. It includes both educational and psychosocial elements and focuses on risk factors as well as resources. The program is carried out in close cooperation with the Center of the Prevention of Addiction (CPA) an established and experienced stakeholder in the field of prevention. The CPA is an experienced local provider of ED specific prevention in schools from the State of Hamburg Institute for Teacher Training and School Development. With this close cooperation we hope to improve the successful implementation and sustainability of the program. An additional aim is to evaluate the prevention program and to do so we have designed a cluster-randomized controlled trial. In this design, the intervention group answers the same questionnaire-set one month before the intervention takes place, immediately afterwards and at a 6-month follow-up. The control group answers the same questionnaire-set at the same time intervals without attending the intervention program.

The study is part of the project psychenet: Hamburg network for mental health which is funded by the German Federal Ministry of Education and Research (BMBF). The purpose of the eleven psychenet sub-projects is to establish innovative care models which aim to improve the prevention, diagnosis and treatment of people with mental illnesses in the Hamburg metropolitan region [36]. Psychenet is coordinated by the Cluster Agency Healthcare Hamburg in collaboration with the University Medical Center Hamburg-Eppendorf. More than 80 scientific and medical institutions, counselling centers, the Senate and the Chamber of Commerce of the Free and Hanseatic City of Hamburg, companies, as well as patients’ and relatives’ associations have been a part of the network since it was initiated in 2011.

Sub-project IX (Health network anorexia and bulimia) focuses on the improvement of the effectiveness and efficiency of ED-specific care. The sub-project is divided into two different intervention arms. This article will provide an overview of the cluster-randomized controlled trial on the prevention of EDs. An overview of the second intervention arm (an intervention focusing on treatment initiation in patients with AN) is described elsewhere [37].

## Methods

### Study design

A cluster-randomized controlled trial was designed to evaluate the efficacy of the prevention program. To this end, global ED risk, and knowledge about EDs as well as values of different ED risk factors are measured one month before, immediately following, as well as six months after the intervention in both conditions of the trial.

### Ethics approval

The study procedure was reviewed and approved by the ethics committee of the Psychotherapist Chamber of Hamburg (approved on the 26th July of 2011) as well as the Hamburg supervisory school authority.

### Study procedures

#### Inclusion and exclusion criteria

Participants need to be adolescents attending school in the 8th or 11th grades (age 14 and 17 years). In addition, written informed consent is required to participate in the study and participants under the age of 16 years are required to provide additional informed consent from parents. Exclusion criteria are insufficient knowledge of the German language as well as not providing informed consent.

#### Recruitment

All secondary school principals within the Metropolitan area of Hamburg are informed about the study purpose and procedure by letters and emails. Participating schools are randomized into the study condition (intervention vs. control) according to the order of application. Randomization is carried out by an external institution (Department of Medical Biometry and Epidemiology, University Medical Center Hamburg-Eppendorf). It is important to note that we were prevented from randomizing according to classes as well as classes switching study condition (e.g. intervention vs. control at the beginning of a new school year) by the Hamburg supervisory school authority. Schools are, therefore, the unit of randomization and they stay in the same condition for the entire study duration.

After randomization school principals are informed to which study condition their school is allocated (intervention vs. control) as well as the detailed study procedure. School principals then nominate suitable classes and propose convenient time slots in the school year. Teachers of participating classes are provided with a detailed schedule of the study and are also given the chance to contact the research team at any time. A letter of consent with study information is distributed to students and their parents two weeks before the study is conducted. These letters contain a detailed description of the study procedure (especially the necessity of randomization). Classes randomized to the control group are given the opportunity to receive the intervention after the completion of the last questionnaire. Study participants have the possibility to contact a psychotherapist from the research team to seek professional mental health help throughout the whole study duration.

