### Methods to reduce bias

Selection bias is minimized by the inclusion of a control group as well as the externally conducted cluster randomization of participating schools. The rate of participants or their parent who refrain from signing an informed consent (i.e. nonresponse rate) will be reported. The full recruitment process will be documented according to CONSORT reporting standards [54]. Surveys with high possibility of intentional misrepresentation (e.g. always choosing the one option of the likert scale) are considered as having dropped out. In addition, data is subjected to an internal validity check.

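### Principals know their school's arm before they choose classes and before families consent, so external randomisation of schools does not protect class and pupil selection

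*Protocol article*

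**What the plan says.** All of the following is in the protocol article.

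- **Unit of randomisation** (Recruitment): "Schools are, therefore, the unit of randomization and they stay in the same condition for the entire study duration".
- **Disclosure** (Recruitment): "After randomization school principals are informed to which study condition their school is allocated (intervention vs. control").
- **Choice of classes** (Recruitment, the next step): "School principals then nominate suitable classes and propose convenient time slots in the school year". Suitability is the only criterion given.
- **Consent** (Recruitment): "A letter of consent with study information is distributed to students and their parents two weeks before the study is conducted". Consent is a condition of entry (Inclusion and exclusion criteria): "Exclusion criteria are insufficient knowledge of the German language as well as not providing informed consent".
- **Assurance** (Methods to reduce bias, opening sentence): "Selection bias is minimized by the inclusion of a control group as well as the externally conducted cluster randomization of participating schools".
- **Partial safeguards.** Methods to reduce bias adds: "The rate of participants or their parent who refrain from signing an informed consent (i.e. nonresponse rate) will be reported". It also promises to document recruitment to CONSORT standards. Statistical analyses adjusts for sex, grade, parental education and individual baseline ChEDE-Q, with school as a random factor.

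**The concern.** In a cluster trial, randomisation balances what was fixed before allocation. Here that is the set of schools. The classes, and the pupils within them, are fixed later, and the person choosing the classes already knows the arm.

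The two arms ask different things of a school. An intervention principal is finding classes for three 90-minute units of a programme on eating disorders. A control principal is finding classes for three rounds of questionnaires. It is plausible, though the article does not say so, that this leads to different choices, for example classes with known body-image problems in one arm and the most cooperative classes in the other.

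If that happens, the arms differ at baseline for reasons that randomisation cannot balance, and part of the primary comparison at six months reflects who was nominated. The Discussion also expects larger effects in a high-risk sample. A different risk mix by arm could therefore change the response to the programme as well as the starting level, and a main-effect baseline covariate does not remove that.

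**Working it through.** **1. Order of events against the assurance**

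| Step | Does the nominating principal know the arm? | Protected by external randomisation of schools? |
|---|---|---|
| School applies and is randomised | No | Yes |
| Principal nominates classes | Yes | No |
| Pupils and parents consent | Yes | No |
| Baseline questionnaire, one month before the intervention (Objectives) | Yes | No |

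The article does not date consent relative to nomination. It does describe nomination first, and the classes have to be known before letters can go to their pupils. A control group does not help in the last three rows, because the question is whether the two arms are filled in the same way.

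**2. The plan's own figures**

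- Detectable difference: 0.3 × 1.14 = 0.342 (females) and 0.3 × 0.61 = 0.183 (males). The plan states 0.34 and 0.18, so they reproduce.
- Design factor: 1 + (65 − 1) × 0.05 = 4.2, and 352 × 4.2 = 1478.4. The plan states 4.2 and 1478, so they reproduce.
- The planned precision is therefore that of 176 independent pupils per arm: SE = √(2/176) = 0.107 SD.

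**3. What baseline adjustment leaves (illustration)**

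Let the arms differ by D (in SD) at baseline and let that difference persist to six months. With baseline-outcome slope b, the adjusted comparison keeps D − b × D = (1 − b) × D.

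The article gives neither D nor b. I assume D = 0.1 to 0.2. For b, I take the retest range of .24 to .44 quoted under ED risk as a low assumption and 0.7 as a high one.

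| b | D = 0.1 | Share of 0.3 | D = 0.2 | Share of 0.3 |
|---|---|---|---|---|
| 0.24 | 0.076 | 25% | 0.152 | 51% |
| 0.44 | 0.056 | 19% | 0.112 | 37% |
| 0.7 | 0.030 | 10% | 0.060 | 20% |

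A difference in something other than the baseline score, such as class motivation, is not covered by this table. Adjustment might remove none of it.

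**4. What a residual shift would do to the test**

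With no true effect and a residual shift s, the two-sided rejection rate is 1 − Φ(1.96 − s/SE) + Φ(−1.96 − s/SE).

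| s (SD) | Rejection rate | Points, females | Points, males |
|---|---|---|---|
| 0 | 5.0% | 0 | 0 |
| 0.05 | 7.6% | 0.057 | 0.030 |
| 0.10 | 15.5% | 0.114 | 0.061 |
| 0.15 | 29.1% | 0.171 | 0.091 |

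**5. Why a school-mean covariate adds something**

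With the plan's ICC of 0.05 and 65 pupils per school, the reliability of a school's mean score is 65 × 0.05 / 4.2 = 0.77. Differences in which classes were nominated appear at this level, and the planned model contains only the individual score.

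**The case against.** - **Bias is not shown.** A reader might infer that bias is built into the trial. The article shows an opportunity for differential selection. It gives no evidence that selection occurred, nor its direction or size. This stands, and the point is limited accordingly.
- **Control classes may have the programme later.** Recruitment offers it to them after the last questionnaire, so a control principal with a worrying class also has a reason to nominate it. This narrows the difference in incentives but does not remove it.
- **Families may not know their arm.** A reader might infer that pupils and parents consent with knowledge of it. The article does not say so. It says that the letters explain the procedure and the need for randomisation. Only the principals' knowledge is established.
- **The assurance is not simply false.** External randomisation does reduce selection at the level of schools, and minimised does not mean eliminated. The sentence needs limiting, not deleting.
- **Safeguards exist.** They are partial. The refusal rate is not stated to be by arm and does not cover class choice. CONSORT documentation records selection but does not prevent it. The covariates correct only what they measure.
- **The percentages rest on assumptions.** The retest range comes without an interval, and it is unclear whether it refers to the subscales or the global score. It need not be the six-month slope in a school sample. This stands, which is why the range extends to 0.7 and is illustrative only.
- **The school authority imposed constraints.** It barred randomising classes and switching conditions. Nothing in the article says that it barred naming classes before allocation.
- **A full protocol may hold nomination rules.** That is possible. But the article itself states the order of steps and draws a conclusion that this order does not support.

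**Conclusion.** The concern holds as an unprotected step in the design and an assurance that reaches too far. Class nomination and consent come after principals know the arm, and the two features credited with minimising selection bias act only on the allocation of schools. The planned covariates would remove part of any imbalance, not all of it.

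The documents do not fix the size or the direction. Under the stated assumptions (D of 0.1 to 0.2 SD that persists, slope of 0.24 to 0.7) the residual is about 0.03 to 0.15 SD, or 10% to 51% of d = 0.3. That should not be read as an estimate of actual bias.

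The registration entry lists recruitment as closed, so the order of steps can probably not be changed for most schools. What remains is honest description, reporting by arm and one sensitivity analysis. This should be fixed, but it does not invalidate the trial.

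**What to change.** **Any school or cohort whose classes are not yet nominated:** have the principal list the participating classes before the biometry department's allocation is released. Time slots can follow, since they depend on the arm. The cost is that principals commit to classes somewhat earlier.

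**Schools already enrolled:**

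1. In Methods to reduce bias, limit the statement to the allocation of schools, and acknowledge that classes and pupils may have been selected after allocation was known.
2. Report by arm the number of eligible and nominated classes, the consent rates and the baseline characteristics.
3. Add a sensitivity analysis of the primary outcome with the school-mean baseline ChEDE-Q as a further covariate alongside the individual score.

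The cost is one extra model, some additional reporting and a less favourable statement on bias. With about 20 schools (the number in the registration title) the school-level coefficient will be imprecise, and the model cannot correct unmeasured differences such as class motivation. The sample size is not affected.

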#### Modules of the intervention

The intervention comprises three 90 – minute units which are delivered over a two week period. The first unit occurs on its own while the second and third units occur straight after each other one week later. The aim of this sequence is to increase the engagement in the prevention program via between session homework. The intervention is administered by four members of the CPA as well as four members of the research team, all of whom follow a detailed manual. All sessions are led by a one member of the CPA and one member of the research team with at least masters’ level degree and a background in clinical psychology. The usual class teacher also attends the sessions. Monthly review meetings are held to ensure that the prevention manual is being implemented to a uniformly high standard through the duration of the study.

#### Unit 1

The first unit begins with brief introduction of the study team and an overview of the prevention program. The first intervention of this unit aims to interactively define the different Western beauty ideals for young females and males as well as the associated positive and negative stereotypes, perpetuating factors and the influence of the media. Therefore, participants are separated into two male and two female groups. One female and one male group each describe what they imagine an ideal young female or male would look like on a poster. Then the results are presented and critically discussed amongst the whole group. The second intervention involves participants rating “How important is it for you to follow beauty ideals?” (0 = not at all, 10 = absolutely) on a visual analogue scale and completing a short checklist of things young people could do to conform to beauty ideals (e.g. physical activity, special clothing, and cosmetics). Female and male participants anonymously mark their answers on the appropriate poster with glue dots. Differences between females and males are then remarked upon and the impact of beauty ideals on everyday life is critically discussed amongst the whole group. Both interventions aim to encourage individual self-reflection on the internalization of Western beauty ideals.

As part of the next intervention, participants watch a five-minute short-film of how models in advertisements are retouched. They are then encouraged to critically discuss how media transferred beauty ideals can be achieved using the things or activities indicated in the checklist if the media manipulates pictures used in advertisements and how the media benefits from the pursuit of beauty ideals.

The last intervention begins with a short recapitulation of the session (collective definition of beauty ideals for females and males, things done to conform to those ideals, role of the media) and then focuses on peer and family pressure. In this process participants provide examples of situations where they felt forced to change something about their body or clothing after comments from others and these examples are written on a large sheet of paper. Particular emphasis is made on the pressure to follow beauty ideals through Facebook and other social media. As homework, participants are asked to watch out for situations in everyday life where there is peer or family pressure and to consider solutions of how someone could react in these situations to positively withstand the pressure from others.

#### Unit 2

After an overview of the previous session, participants pass through an eleven station multi-methodological circuit in pairs. An evaluation sheet is handed out to each participant before the beginning of the circuit. This serves to monitor whether participants pass every station and how every station is evaluated (e.g. “Did you learn something relevant about yourself at this station? Did you learn something new at this station?”). Participants change stations every eight minutes and mark their answers on the evaluation sheet before moving onto the next station. At station 1, participants listen to a short mindfulness exercise to improve body perception on an mp3 player. Then they mark body parts they like, appraise as neutral or dislike on gender adapted figures. Station 2 aims to help participants identify their own resources. Different things which may help someone be self-confident are listed on a worksheet and participants are encouraged to find own examples. Participants then write the three most important resources to them on a small card. This card is then used later at station 3. There, participants find a wide choice of pictures showing positive activities one can do to cope with negative emotions. Things which the participants think might be helpful for them should be written on the backside of the small card. At station 4, participants take pictures of each other and critically discuss in pairs how they present themselves in social media. Station 5 comprises a puzzle about the physical consequences of different EDs. Participants find pictures of different body parts (e.g. liver, skin, hair) and need to find the corresponding written information. The solution is available at the end. At station 6, participants note the food they would eat on a typical school day and then discuss whether their nutrition is in line with the German Association of Nutrition’s guidelines [38]. Participants can also get ideas on how nutrition can be improved by looking at a wide range of pictures of healthy food. Station 7 begins with a short audio sequence in which a boy visits his GP and the set-point theory is explained. Afterwards, participants complete a cloze text task. A solution word helps participants check whether all given answers are correct. At station 8, a counter-attitudinal role-play based on the homework from unit 1 is conducted. Each participant attempts to dissuade one of the group leaders from succumbing to peer or family pressure. At station 9, participants find gender-adapted descriptions of difficult situations as well as three respective coping strategies. The positive and negative consequences of each coping strategy are evaluated in pairs and participants are encouraged to choose a usable one. Station 10 involves a reciprocal interview on good reasons for and examples of healthy physical activity. Station 11 is the last of the circuit and includes an exercise to mindfully enjoy a piece of chocolate.

#### Unit 3

This unit begins after a regular school break. After re-entering the classroom participants are separated into three groups and each group is allocated one of three eating disorders (AN, BN or BED). A film is presented which shows three young people suffering from one of the EDs and group participants collect risk factors and symptoms described in the film about their allocated ED. Results are then presented to the whole class. Afterwards the groups are encouraged to reflect how they would react to and could support a person with an ED in their own class. Results are again presented to the class and the reduction of stigma of EDs is emphasized. After that, prior knowledge about treatment options for EDs and other mental illnesses is discussed and a group leader from the CPA provides the participants with information about ED-specific counselling-centers, psychotherapy as well as treatment options for different EDs. Participants are then able to pose any questions. The unit ends with a recapitulation of the whole prevention project and participants are encouraged to formulate their “lessons learned” during participation. After that, participants are asked to complete the post intervention questionnaire-set and are told that there would be a follow-up in six months. In addition to the post intervention questionnaire, a flyer is distributed in both study conditions (intervention and control) which includes the contact information of different treatment centers for EDs and other mental illnesses. Participants are invited to use information contained in the flyer if they feel that they themselves or a friend is in need of professional mental health help.

